#### Phase 2: Training provision

Training will be given to both traditional and modern care practitioners in three different rounds. In the first round, traditional practitioners (traditional healers and religious leaders) will be trained for 5 days. Two days of training will be given to healthcare providers (TB focal persons) in the second round, and 1-day training will be carried out in the third round at the end of the sixth month after the first round of training. The training will be given by researchers and a person having training of trainers [4] certificates at the regional health bureau. Participants that can score 75% on the post-test in the knowledge and attitude domains and are skilled in practice will be considered part of the intervention team. A pilot test will be conducted outside the study area on 5% of the project sample size based on Connelly suggestion [31]. Based on the pilot findings and experts’ judgment, the intervention package will be refined. Before the actual intervention implementation, baseline data will be collected and analyzed.

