### Randomization and recruitment

Randomization will be done at the district level. There are thirteen districts and two town administrations. Among a total of districts and town administrations, six districts and/or town administrations in South Gondar Zone will be selected using the random.org software by considering the rule of thumb assumption that covers 40% of districts and town administrations. Thus, the selected districts/town administrations will be assigned to the intervention and control arms with a 1:1 allocation ratio. This means three districts or town administrations will be randomly assigned to the intervention arm, and the other three districts or town administrations will be assigned to the control arm. District or town size will not be considered in the randomization process. All health facilities in the intervention and control arms fulfilling the eligibility criteria will be included in the study. The eligibility criteria for the inclusion and/or exclusion of health facilities will be based on the availability of TB diagnostic and treatment services, including the microscope diagnostic service and DOT programs. Participants will recruit to the study when confirmed they have any form of TB and are registered to the DOT programs. Participants will enter into the trial individually based, and patients will recruit continuously until the desired sample size achieve. Recruitment of participants will be from July 1 to September 30, 2022. The statistician who allocated the intervention and control arms, an expert who assesses the outcomes, participants who will be assigned to intervention and control arms, and healthcare providers who provide TB care will not be aware of who were assigned to the intervention and control arms. The project manager and/or investigators will be unblinded.

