### Data collection

Data will be collected on the dependent variables (i.e., case detection, diagnosis delay, and cost of TB care) and independent variables (i.e., socio-demographic, health-seeking behavior variables, patient knowledge of TB, healthcare accessibility, distance, contact history, and support). Secondary data will be collected from the patient’s medical records, and primary data will be collected using a structured questionnaire adapted from previous literature. The structured questionnaire is composed of socio-demographic and economic factors, health-seeking behaviors, patient knowledge, service accessibility, stigma, contact history, the catastrophic cost of TB, diagnosis delay, and healthcare initiation. The questionnaire will be translated into the national language (Amharic) spoken by almost all residents in the study area. The data will be collected using face-to-face interview questionnaires. The data will be collected by BSc nurses or public health officers who had data collection experience. Nurses or public health officers who had MSc/MPH degrees will be selected for data collector supervisors. The data will be collected at baseline and at the end of 1 year of the intervention.

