### Data analysis

Descriptive statistics will be used to summarize the baseline data. A chi-square test will be performed to compare the baseline characteristics of the intervention and control groups. Comparisons of detection rate, diagnosis delay, and costs of TB care between and within the intervention and control groups will be done using independent samples and paired sample *t*-tests, respectively. The independent *t*-test will be also used for the knowledge and attitude of post-test results of practitioners.

Logistic regression analysis will be used to determine the factors associated with case detection rate and diagnosis delay. A univariable logistic regression model will be fitted, and variables having a *p*-value less than 0.25 in the univariable logistic regression model will be fitted into the multivariable models. Variables with a *p*-value < 0.05 in the multivariable logistic regression model can be considered statistically significant. Crude and adjusted odds ratio (OR) with 95% confidence interval (CI) will be calculated to measure the strength of association between the dependent and independent variables. The fitness of the logistic regression model will be checked using the Hosmer–Lemeshow goodness of fitness test at *p*-value > 0.05. Multicollinearity between explanatory variables will be checked by a variance inflation factor (VIF), and variables with a VIF > 5 will be excluded from the final models.

Generalized linear mixed models (GLMM) will be used to assess the impact of the intervention on the change of cost of TB care. This GLM enables us to accommodate the correlation of observations due to the pre and post-intervention measurements and clustering of individuals within randomly selected clusters. Model fitting will be checked before the analysis is done. The effects of potential confounding factors will be controlled. The variance of the cluster-level residual errors will be computed using the intercept-only model. The variation between and within the groups will be analyzed.

Subgroup analysis will be employed to explore whether there is evidence that the detection variation depends on certain patients or facility characteristics. Covariate adjusted analysis will also employ to refine the analysis of case detection variation in the intervention and control arms the fact that some baseline characteristics may be related to outcome and unbalanced between the groups.

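### Paired t-tests are planned for diagnosis delay and cost of TB care, but each patient has only one delay and one episode cost, so no patient-level before-and-after pairs exist

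*Protocol article*

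**What the plan says.** All references are to the protocol article.

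- **Data analysis, tests.** Detection rate, delay and cost are compared between and within the two arms, and this "will be done using independent samples and paired sample *t*-tests, respectively". The paired test is thus the within-arm, before-and-after test for all three outcomes. Its unit (patient, facility or district) is not given.
- **Data analysis, model.** A generalized linear mixed model assesses the intervention's impact on the change in cost. It is meant to "accommodate the correlation of observations due to the pre and post-intervention measurements" and, in the same sentence, to allow for the clustering of individuals.
- **Randomization and recruitment.** "Participants will recruit to the study when confirmed they have any form of TB and are registered to the DOT programs". Entry is individual, and "patients will recruit continuously until the desired sample size achieve". Three districts or town administrations go to each arm.
- **Phase 2: Training provision.** "Before the actual intervention implementation, baseline data will be collected and analyzed".
- **Data collection.** "The data will be collected at baseline and at the end of 1 year of the intervention".
- **Outcomes of interest and Appendix 2.** Delay starts with symptoms and stops at diagnosis. The numerator for catastrophic cost is a single sum covering the illness from first symptoms until treatment ends. The case detection rate is notified cases over estimated cases for the year, a ratio for an area.

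**The concern.** A paired t-test needs two values of the same quantity on the same unit. For delay and cost the natural unit is the patient, and the protocol's own entry rule and outcome definitions give each patient one value. A statistician following the text would find nothing to pair, or would pair unrelated patients by file order. The second course produces a p-value with no design behind it, which treats patients as independent although they come from three districts per arm whose levels may move between periods. The cost model raises a related doubt: it lists a pre/post correlation apart from clustering, without saying whether this correlation belongs to the patient or to the district. Two of the three trial outcomes, both secondary, are affected.

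**Working it through.** **Step 1. Can one patient supply two values?**

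| Outcome | When the value is complete | Second value after the intervention? |
|---|---|---|
| Diagnosis delay | At diagnosis, so already at entry | No |
| Catastrophic cost | At the end of treatment, one total per episode | No; a later interview only completes the same total |
| Case detection rate | Per area and year | Yes, the same district in two periods |

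A patient in the baseline round was diagnosed before the intervention began and cannot provide a post-intervention delay for that episode. A recurrence within the year is conceivable, but nothing in the protocol plans for one. No section describes re-measuring baseline patients or linking patients between rounds.

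**Step 2. Do the stated sample sizes contain a pre/post correlation?** Inputs from Sample size determination: 59.9% against 45.9% for delay, 40% against 27% for cost, alpha 0.05 (two-sided assumed), power 80%, non-response 10%. With pooled variance under the null and no continuity correction,

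n per arm = [1.960·√(2p̄(1−p̄)) + 0.842·√(p1(1−p1)+p2(1−p2))]² / (p1−p2)².

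- Delay: (1.3836 + 0.5882)² / 0.0196 = 3.888 / 0.0196 = 198.4, so 199 per arm and 398 in total; 398 × 1.10 = 437.8, matching the stated 438.
- Cost: (1.3083 + 0.5564)² / 0.0169 = 3.477 / 0.0169 = 205.7, so 206 per arm and 412 in total; 412 × 1.10 = 453.2, matching the stated 453.

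Both figures follow from two independent samples. No pre/post correlation enters, and no sample size changes because of this point.

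**Step 3. What would pairing claim that is not there?** With n values per period and standard deviation SD, the variance of a within-arm mean change is 2·SD²·(1−ρ)/n, before any district effect. Different patients give a patient-level ρ of 0. Assumed values of 0.3, 0.5 or 0.7 would cut the variance to 0.7, 0.5 or 0.3 of its size, a gain that is not available here.

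**Step 4. What happens if arbitrary pairs are used?** A simulation with no true change took 3 districts, 71 patients per district and period (about 214 per arm, the stated cost figure, assumed to apply in each period), normal outcomes and 4,000 runs per setting. The intracluster correlations (ICC) are the protocol's: 0.03 for the detection rate, and 0.05, the between-centre value in the delay and cost calculations. The cluster autocorrelation (CAC; how far a district keeps its level between periods) is an assumption. As a hand check, the true variance of the change relative to the naive one is roughly F = (1−ICC) + 71·ICC·(1−CAC), and the type I error is roughly 2·[1−Φ(1.96/√F)].

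| ICC | CAC | F | Hand check | Simulated |
|---|---|---|---|---|
| 0.03 | 1 | 0.970 | 4.7% | 5.2% |
| 0.03 | 0.8 | 0.970 + 0.426 = 1.396 | 9.7% | 10.1% |
| 0.03 | 0.5 | 0.970 + 1.065 = 2.035 | 16.9% | 18.3% |
| 0.05 | 1 | 0.950 | 4.4% | 4.5% |
| 0.05 | 0.8 | 0.950 + 0.710 = 1.660 | 12.8% | 13.0% |
| 0.05 | 0.5 | 0.950 + 1.775 = 2.725 | 23.5% | 25.0% |

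The excess comes from district shifts, not from the arbitrary pairing, which by itself makes the result depend on file order. In one simulated data set, re-ordering the pairs moved p between 0.149 and 0.206 (central 95% of orderings), against 0.178 for the independent-samples test.

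**Step 5. Pairing by district.** Paired tests on the three district means of an arm kept about 5% error in every setting, but have 3 − 1 = 2 degrees of freedom (critical t 4.30). Comparing the six district changes between arms has 3 + 3 − 2 = 4 (critical t 2.78).

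**The case against.** **The unit is not stated.** District or facility means of delay and cost could be paired as detection rates can, so to say that no paired test of any kind can be run would be too strong. This stands, and it limits the point to patient-level pairs. The text nevertheless names delay and cost alongside the detection rate without any step that reduces them to district means.

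**Different patients is an inference.** No sentence says so, and Trial adherence and retention strategies speaks of attrition and follow-up, which suggests a cohort. The independent-samples formulas concern the contrast between arms and do not settle how the two rounds are linked. Both remarks are fair. But a followed cohort would still yield no second delay and no second episode total.

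**The mixed model.** A reader might infer that the cost model assumes within-patient correlation and that its standard error is wrong. The document does not support that. The sentence also names clustering of individuals and never mentions a within-patient correlation; correlation of the same district across periods is a natural reading. Random-effect structure is detail that an analysis plan may hold. What remains is an ambiguity.

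**Within-arm significance.** A reader might also infer that an effect will be declared when one arm changes significantly and the other does not. The protocol contains no such rule. The Abstract, Phase 4, Control groups and Data analysis all compare the arms.

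**Conclusion.** The point holds in a limited form. For diagnosis delay and cost of TB care, the paired t-test cannot be a patient-level test under the protocol's own entry rule, outcome definitions and timing, and as written it is the wrong test. The case detection rate, the primary outcome, is not touched: it can be paired by district, with three pairs per arm.

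The type I error range of about 10% to 25% applies only if arbitrary pairs are formed and districts shift between periods; it rests on assumed autocorrelations of 0.8 and 0.5 and on about 214 patients per arm in each period. With no shift the error stays near 5%. The degrees of freedom take the six districts as the randomised units, as Randomization and recruitment states; the 40 clusters in the sample size section are not used here.

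This should be corrected before analysis, but it concerns secondary outcomes and changes no sample size and no data collection.

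**What to change.** 1. State that the baseline and one-year data on delay and cost are independent cross-sections of patients within the same districts.
2. Delete the patient-level paired t-tests for these two outcomes. A paired comparison of detection rates may stay if the district is named as its unit.
3. Base the intervention effect on the between-arm difference in change. Either compare the six district-level changes between arms, or fit an arm-by-period term in a mixed model that accounts for district and district-by-period clustering, with a small-sample correction. With six districts the variance components will be poorly estimated, so the simpler comparison is a reasonable choice.
4. Add that the pre/post correlation in the cost model is between periods within a district, not within a patient.

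The cost is wording only. The within-arm p-values for delay and cost are lost, and inference rests on few degrees of freedom (4 for the six-change comparison). That reflects the number of randomised districts.

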#### Sample size calculation for TB detection rate

Since the case detection rate will be calculated by considering the WHO estimator for the year 2023 per 100,000 populations. Estimating the number of TB cases for that year will be computed by using total cases in the year/100,100 * total population found in the catchment area multiplied by 100, expressed as a percentage. Therefore, all cases that are confirmed as TB patients in the selected districts will be considered as the final sample size.

The number of clusters involved in the study was determined using the following formula [39]: The number of clusters (*K*) required in each arm for unequal cluster sizes was also determined using the formula [40]: *K* = *n* [1 + ((CoV2 + 1) *m* − 1) ICC]/*m*′], where Cov2 = coefficient of variation of 0.25, effective ICC value of 0.03 for cluster-level ICC value of TB detection rate, *n* = sample size under individual randomization, *m* = average number of individuals found in each cluster was 18. From 40 clusters, with unequal clusters for intervention and control arms, 24 clusters included in the intervention, and 16 clusters in the control arm.

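### As described, the mixed model for change in cost names no district-by-round component; fitted with a district intercept only, its interval would be too narrow

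*Protocol article*

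**What the plan says.** All references are to the protocol article.

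- **Model and target** (Data analysis): "Generalized linear mixed models (GLMM) will be used to assess the impact of the intervention on the change of cost of TB care".
- **Correlation handled** (same section): the model is to "accommodate the correlation of observations due to the pre and post-intervention measurements and clustering of individuals within randomly selected clusters".
- **Cluster-level variance** (same section): "The variance of the cluster-level residual errors will be computed using the intercept-only model". No other cluster-level variance is mentioned, and the random effects of the analysis model are not listed.
- **Timing** (Data collection): "The data will be collected at baseline and at the end of 1 year of the intervention". Phase 4 of the intervention section describes comparing end-line with baseline outcomes, cost included, between the arms.
- **Unit of randomisation** (Randomization and recruitment): "Randomization will be done at the district level"; "three districts or town administrations will be randomly assigned to the intervention arm", and the other three form the control arm.
- **Who is measured** (Randomization and recruitment; Appendix 2): patients enter once TB is confirmed and they are registered for treatment. Catastrophic cost covers one episode, from first symptoms to the end of treatment.
- **A different cluster count** (Sample size calculation for TB detection rate): "24 clusters included in the intervention, and 16 clusters in the control arm", where the "average number of individuals found in each cluster was 18".

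**The concern.** Patients enter at diagnosis and cost is counted over one episode, so the baseline and one-year rounds would consist largely of different people. What then links the rounds is the district. A single random intercept per district describes a level that is the same in both rounds. When change is compared between arms, that level is subtracted out, and the standard error rests on scatter between patients.

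Districts need not move in step over a year. Transport fares may rise, supplies may run short, or a facility may open in one district and not in others. Such shifts enter the difference between three intervention and three control districts. In a model without a district-by-round term they do not enter its standard error.

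At stake is the 5% level for the cost outcome. Three districts that happened to move together could give a significant change in cost with no intervention effect.

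**Working it through.** **1. The plan's own figure.** Inputs from the cost sample size section: 40% against 27%, two-sided 5%, power 80%, 10% non-response. The two-proportion formula without continuity correction gives

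n = [1.96·√(2·0.335·0.665) + 0.8416·√(0.40·0.60 + 0.27·0.73)]² / 0.13² = 205.8, so 206 per arm and 412 in total.

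412 × 1.10 = 453.2, which reproduces the stated 453. The plan then multiplies by 0.95: 453 × 0.95 = 430.35, against 428 stated. I use 428.

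**2. Patients per district per round (m).** The article does not say whether 428 applies to each round or to both together.

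- Each round: 428/6 = 71.3.
- Both rounds together: 428/12 = 35.7.

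**3. Intraclass correlation (ICC).** The cost sample size section uses 0.05 and the detection rate section 0.03. Both are borrowed here: the first comes from sizing a binary cost outcome, the second from another outcome.

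**4. Between-round correlation of a district's effect (cluster autocorrelation, CAC).** Not in the documents. I assume 0.5 to 0.9 and show 1.0 for reference.

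**5. Variance ratio.** Set total variance to 1. Patient variance is 1 − ICC and district-by-round variance is ICC·(1 − CAC). With J districts per arm, the difference in changes has

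- true variance 4·[ICC·(1 − CAC) + (1 − ICC)/m]/J;
- variance under a district-intercept-only model 4·[(1 − ICC)/m]/J.

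Ratio R = 1 + m·ICC·(1 − CAC)/(1 − ICC). J cancels, so more districts would not remove the problem.

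False-positive rate at nominal 5% = 2·[1 − Φ(1.96/√R)].

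Two cases in full:

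- m = 71.3, ICC 0.05, CAC 0.5: R = 1 + 71.3·0.05·0.5/0.95 = 2.876; 1.96/√2.876 = 1.156; rate 24.8%.
- m = 35.7, ICC 0.03, CAC 0.9: R = 1 + 35.7·0.03·0.1/0.97 = 1.110; 1.96/√1.110 = 1.860; rate 6.3%.

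| m | ICC | CAC 1.0 | CAC 0.9 | CAC 0.8 | CAC 0.5 |
|---|---|---|---|---|---|
| 35.7 | 0.03 | 5.0% | 6.3% | 7.6% | 11.6% |
| 35.7 | 0.05 | 5.0% | 7.2% | 9.5% | 15.9% |
| 71.3 | 0.03 | 5.0% | 7.6% | 10.3% | 17.6% |
| 71.3 | 0.05 | 5.0% | 9.5% | 13.9% | 24.8% |

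**6. Simulation check** (40,000 runs per setting, normal outcome, three districts per arm). With m = 71 and ICC 0.05, rates are 4.9%, 9.7%, 13.5% and 24.3% for CAC 1.0, 0.9, 0.8 and 0.5. With m = 36 and ICC 0.03 they are 5.0%, 6.1%, 7.5% and 11.8%. These agree with the formula.

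**7. If the 40 clusters were the units.** Take m = 428/40 = 10.7 or the stated average of 18, with each cluster shifting independently. At m = 10.7, ICC 0.03, CAC 0.9 the rate is 5.4%; at m = 18, ICC 0.05, CAC 0.5 it is 10.6%. The range is about 5% to 11%.

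**8. With the term added.** Testing arm-by-round against the scatter of the six district changes, on 6 − 2 = 4 degrees of freedom, gives 4.7% to 5.1% in every setting simulated. With the term but a normal reference distribution, the rate is about 4% to 10%, so the degrees of freedom must be stated too.

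**The case against.** The strongest objection is that the defect is inferred. The article does not list the random effects, and neither names nor rules out a district-by-round term. The sentence on the intercept-only model describes a null model and does not fix the random part of the analysis model. A journal article may leave that list to an analysis plan that is not shown. This stands against any statement that the plan definitely omits the term. It does not dispose of the point: the article does state which correlations the model handles, and that list does not cover what a change comparison across six districts needs. The sample size sections for delay and cost also call the trial individually randomised, so the right structure cannot be presumed to sit elsewhere.

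Second, the Abstract speaks of comparing arms with adjustment for baseline differences. An end-line comparison of that kind would keep the district intercept in the error term. That is a fair reading, and the point is limited to a baseline-to-end-line contrast, which is what the Data analysis section and Phase 4 describe for cost.

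Third, paired t-tests and talk of attrition suggest that the same people might be measured twice. The entry criterion and the per-episode cost point the other way, but the article is not explicit. If some patients did appear in both rounds, a district intercept would still cancel from the change.

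Fourth, the 40 clusters would lower the rate. They would do so only if clusters within a district shift independently; a shift shared across the district would still be missed.

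Finally, cost is a secondary outcome, and this is the one analysis that explicitly accounts for clustering. That bears on priority.

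**Conclusion.** The point holds in conditional form. As described, the cost model names no district-by-round component. If it is built with a district intercept only and used for the change from baseline to end-line, its standard error leaves out district shifts between rounds.

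Under the assumptions shown (CAC 0.5 to 0.9, ICC 0.03 to 0.05, 36 to 71 patients per district-round, roughly normal outcome), the false-positive rate is roughly 6% to 25% against a nominal 5%. It is 5% if district effects are fully stable, and about 5% to 11% with 40 independently shifting clusters.

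A reader might infer three stronger things, and the documents support none of them:

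- **That the plan certainly has a single cluster-level variance.** The random effects are not listed.
- **That a particular inflated error rate is established.** Every figure above 5% depends on a CAC that the documents do not give.
- **That district shifts bias the effect.** Under randomisation they do not; they make the interval too narrow.

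This is an inexpensive improvement to a secondary analysis that should be made before the data are analysed.

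**What to change.** In the Data analysis section, for any baseline-to-end-line comparison of cost, specify:

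- fixed effects for arm, round and arm-by-round;
- random effects for district and for district-by-round;
- arm-by-round tested on 4 degrees of freedom (six districts minus two arms).

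An equivalent and simpler choice is to compute one change per district and compare three against three, also on 4 degrees of freedom.

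State in the same place that the cluster is the randomised district, and reconcile this with the 40 clusters in the sample size section for detection rate.

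The change takes a few sentences and no new data. Its cost is a wider interval for the cost effect.
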